
### Objectives {7}

The *overall objective* of this randomized controlled trial is to examine if low load BFR-T can prevent muscle atrophy or mitigate its progression by studying changes in muscle mass and muscle signaling in patients with resectable pancreatic, biliary tract, or liver cancer.

Using a two-armed randomized controlled trial *the primary aim* of this project is to assess if a BFR-T program can preserve or increase skeletal muscle mass measured as thickness and cross-sectional area in patients with resectable pancreatic, biliary tract, or liver cancer.

The *secondary aims* are to investigate the effects of BRF-T on:Myogenic stem cells, mitochondrial function, capillarization, macrophage infiltration, and muscle catabolism, measured in skeletal muscle biopsies from a subgroup of voluntary participantsMuscle strength, physical function, body composition, and physical activity levelsSelf-reported fatigue, health-related quality of life (HRQoL), and nutritional statusThe patients’ experience of the exercise programHospitalization, prognostic markers, and different blood status concentrations

The use of BFR-T using low training loads may allow for a quick postoperative recovery by avoiding the high levels of mechanical muscle stress typically associated with high-load resistance exercise. Thus, BFR-T could serve as a feasible exercise modality in this patient population to mitigate the burden of cachexia. Moreover, the metabolic stress induced by BFR-T may have the potential to normalize the disrupted intramuscular milieu in cachectic muscle leading to a proper muscle regenerative response. Therefore, it is expected that the challenge imposed by BFR-T will:Stimulate muscle hypertrophy and thereby preserve or increase muscle massInduce beneficial effects on skeletal muscle characteristics in terms of myogenic stem cell count and differentiation, basal autophagy activity, mitophagy/biogenesis, capillaries per muscle fiber, macrophage infiltration, and reduce the levels of catabolic markersImprove muscle strength, physical function, and physical activity levelsCounteract an increase in self-reported fatigue and a decline in HRQoLDue to its proposed positive effects on skeletal muscle mass and quality, lead to lower hospitalization rates

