### Secondary outcomes

➢ Skeletal muscle molecular characteristics will be assessed in skeletal muscle vastus lateralis biopsy tissues from participants included in the study who agree to undergo the biopsy procedure (only at the Norwegian site: T0, T3).
◦ Myogenic stem cell count◦ Autophagy◦ Capillary number per muscle fiber◦ Macrophage infiltration◦ Markers of skeletal muscle catabolism➢ Patient-reported outcome measures (T0, T1, T2, T3, T4)◦ Self-reported fatigue assessed by means of the validated European Organization for Research and Treatment of Cancer Fatigue questionnaire (EORTC QLQ-FA12).◦ Health-related quality of life (HRQoL) assessed by means of the validated Quality of Life Core Questionnaire (EORTC-QLQ-C30)◦ Nutritional status will be assessed by means of the validated Patient-Generated Subjective Global Assessment scale (PG-SGA).➢ Physical fitness/performance/activity
◦ Physical function determined by the short physical performance battery and a submaximal and maximal (ramp) cycle test to evaluate cardiorespiratory fitness and maximal isometric muscle strength evaluated in a standardized manner (T0, T1, T2, T3)◦ Objectively measured physical activity and sedentary behavior using the Fitbit activity monitor (T0, T1, T2, T3, T4)➢ Clinical outcomes will be recorded retrospectively from the patient’s medical records (T4)
◦ Hospitalization rates◦ Blood status➢ Vital signs and anthropometrics
◦ Body composition using bioimpedance analysis (T0, T1, T2, T3)◦ Body composition using dual x-ray absorptiometry (only at the Norwegian site: T0, T3)◦ Body composition will also be measured using computed tomography (CT) scans when performed as a routine measurement for the patients (T0, T4). Thus, no extra CT scans will be conducted for the purpose of this study to minimize exposure to radiation.➢ Explorative outcomes

Patient’s experience of the exercise program, protein supplement, and activity tracker through focus group or individual interviews will take place sometime following the exercise intervention for a voluntary subset of the included participants in the exercise group.

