### Sample size {14}

To achieve 80% power at an alpha level of 0.05 (two-tailed) from pre- to post-intervention based on a magnitude of change of 1 mm in skeletal muscle thickness [13], and a standard error of measurement of 0.8 mm [14], a total of 42 participants are required. According to previous findings [5], we anticipate that 25% of the participants may drop out of the study; therefore, a total of 52 participants will be required to confirm or refute our hypothesis.

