Self-reported fatigue will be assessed by means of the validated EORTC Fatigue questionnaire EORTC QLQ-FA12 [16, 17]. The EORTC QLQ-FA12 is a multidimensional instrument that measures various aspects of cancer-related fatigue, including overall, physical, emotional, and cognitive aspects. Fatigue scores obtained from the questionnaire are transformed into scales ranging from 0 to 100. Higher scores on the scales indicate a higher level of cancer-related fatigue. Missing data will be handled according to the guidelines provided in the EORTC scoring manual.HRQoL will be assessed by means of the validated EORTC-QLQ-C30 [15]. The EORTC QLQ-C30 is a 30-item questionnaire that assesses the quality of life in cancer patients with five multi-item functional scales (physical, role, cognitive, emotional, and social); one global quality of life scale; three symptom scales (fatigue, pain, and nausea/vomiting) and six single-items measuring symptoms common among patients with cancer in general (dyspnea, insomnia, appetite, constipation, and diarrhea) and financial impact. The HRQoL scores will be transformed into a scale ranging from 0 to 100 where higher scores for function and/or global QOL correspond to better HRQoL, while higher scores for symptoms represent worse problems. Missing data will be handled according to the guidelines provided in the EORTC scoring manual.Nutritional status will be assessed by means of the PG-SGA scale [18]. The PG-SGA has four components, nutritional status, the physical examination, disease/condition and metabolic demand assessment components, and medical history component (comprising weight history, food intake, nutrition impact symptoms, as well as activities and function component). All four components are self-reported by patients. A total score is calculated by summing the scores from the four components, where higher scores indicate worse nutritional status.Physical function will be assessed by the short physical performance battery that includes the side-by-side stand (10 s), the semi-tandem stand (10 s), tandem stand (s), gait speed test (s), and chair stand test — 5 times (s). A total score will be calculated for the battery of tests included in short physical performance. Muscle strength is being assessed by a hydraulic hand dynamometer (JAMAR, SAEHAN corporation, Chang-won, S. Korea), and isometric muscle strength tests measuring upper and lower limb muscle strength by leg extension and chest press using a power meter (Swedish site: HUR, Ab HUR Oy, Kokkolac, Finland. Norwegian site: Gym2000, Vikersund, Norway; Strain gauge: U2A 200, Hottinger Baldwin Mestechnik, Darmstadt, Germanuý (custom made amplifier); data acquisition: Labview, National Instruments, TX, USA (custom built)). Cardiovascular fitness is assessed, both predicted and maximal oxygen uptake (VO_2peak_), through the validated sub-maximal Ekblom-Bak test [19] and a ramp test on a cycle ergometer to exhaustion which has been shown to accurately predict VO_2peak_ [20], (LODE, Lode BV, Groningen, The Netherlands).

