### Plans for collection, laboratory evaluation, and storage of biological specimens for genetic or molecular analysis in this trial/future use {33}

Biological material will be collected in the form of biopsy material (muscle), plasma, and serum. The material will be stored in a project-specific research biobank at the Norwegian School of Sport Sciences. A small amount (≈100 mg) of muscle tissue will be obtained by the percutaneous needle technique under local anesthesia [21]. The muscle biopsy will be immediately snap frozen in liquid nitrogen and the samples will then be stored in – 80° until used for immunohistochemistry (5–10 μm sections will be cut and stained for relevant markers for capillaries per muscle fiber, satellite cell content, and macrophage infiltration), and protein quantification (samples will be determined for protein concentration by a protein assay, and immunoblotting will then be performed using relevant antibodies for markers of autophagy, mitophagy, and muscle catabolism) [22]. Blood samples (approximately 10 mL) will be collected and then analyzed with proteomics and metabolomics methods.

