## Statistical methods

### Statistical methods for primary and secondary outcomes {20a}

Data will be analyzed using the IBM SPSS (Statistical Package for the Social Sciences) 26 statistical package for Windows (SPSS, Chicago, IL, USA). For the quantitative analysis, descriptive statistics, ANOVA, and chi-squared tests will be used to describe and compare baseline characteristics. For longitudinal analysis, linear mixed modeling adjusted for baseline values (T0) of the outcome will be used to detect any significant differences between the two groups from pre- to post-intervention as well as at follow-up 6 months following surgery. Group-by-time interaction will be included as a fixed effect. Corresponding effect sizes will also be calculated. Chi-squared tests and corresponding odds ratios will be calculated for hospitalization rates. All tests will be 2-tailed and statistical significance set at *p* ≤ 0.05.

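### The p ≤ 0.05 rule covers every secondary test, with no order, gate on the primary or exploratory status, so a false secondary finding is far more likely than 5%

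*Protocol article*

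**What the plan says.** The analysis section {20a} is headed for primary and secondary outcomes alike. It plans linear mixed models for "differences between the two groups from pre- to post-intervention as well as at follow-up 6 months following surgery", chi-squared tests for hospitalization, and one criterion for all of them: "All tests will be 2-tailed and statistical significance set at" p ≤ 0.05.

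The Objectives {7} state directional expectations for muscle markers, for strength, function and physical activity, and for fatigue and quality of life. They also expect the training to "lead to lower hospitalization rates".

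The Secondary outcomes list names biopsy markers, patient-reported outcomes, fitness and activity, clinical outcomes and body composition. Many are measured repeatedly, for example "Patient-reported outcome measures (T0, T1, T2, T3, T4". Study instruments {18a} then splits the questionnaires into scales. For the QLQ-C30 it lists five functional scales, a global scale and "three symptom scales (fatigue, pain, and nausea/vomiting) and six single-items measuring symptoms common among patients with cancer in general", plus financial impact as one of the six single items. The specimen section {33} adds: "Blood samples (approximately 10 mL) will be collected and then analyzed with proteomics and metabolomics methods".

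Among the listed outcomes, only the patient interviews are called explorative. The additional-analyses section {20b} uses the language of exploration only for moderators and mediation.

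**The concern.** The authors use an exploratory label and do not apply it to the tested secondary outcomes. Read as written, a secondary p-value at or below 0.05 meets the protocol's own criterion for a significant effect, often for an expectation stated in advance, whatever happens to the primary outcome.

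The trial plans 52 patients and is sized on muscle thickness alone. If the primary result is negative and one fatigue, strength or hospitalization comparison falls below 0.05, the report could call that a significant effect under the plan. A reader would have no means of telling it from the chance result that a family of this size often produces.

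**Working it through.** **The plan's own alpha.** The Sample size section {14} reads "To achieve 80% power at an alpha level of 0.05 (two-tailed) from pre- to post-intervention", with a "magnitude of change of 1 mm in skeletal muscle thickness" and a standard error of measurement of 0.8 mm. If the SD of a change is taken as 0.8 × √2 = 1.131 mm, then n per arm = 2 × (1.960 + 0.842)² × 1.131² / 1² = 20.1, rounded up to 21, or 42 in total, as stated. This only confirms that 0.05 two-sided was the level for one muscle-thickness comparison. Section {20a} applies the same level to every other test.

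**Counting the secondary endpoints at one contrast.**

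| Domain | By outcome | By scale or test |
|---|---|---|
| Biopsy markers | 5 | 5 |
| Fatigue (QLQ-FA12) | 1 | 4 |
| Quality of life (QLQ-C30: 5 + 1 + 3 + 6) | 1 | 15 |
| Nutritional status (PG-SGA) | 1 | 1 |
| Physical performance battery | 1 | 1 |
| Cardiorespiratory fitness | 1 | 2 |
| Strength (grip, leg extension, chest press) | 1 | 3 |
| Activity and sedentary behavior | 2 | 2 |
| Hospitalization, blood status | 2 | 2 |
| Body composition (three methods) | 3 | 3 |
| **Total** | **18** | **38** |

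**Chance of at least one p ≤ 0.05 when there is no effect.** For k independent tests this is 1 − 0.95^k in either direction and 1 − 0.975^k in favour of the training. For test statistics with common correlation ρ and c = 1.96, the either-direction figure is

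1 − ∫ [Φ((c − √ρ·x)/√(1−ρ)) − Φ((−c − √ρ·x)/√(1−ρ))]^k φ(x) dx.

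The figure favouring the training drops the second Φ term. The document gives no correlations, so ρ is an assumption and is shown as a range.

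| k | ρ | Either direction | Favouring BFR-T |
|---|---|---|---|
| 18 | 0.5 | 0.40 | 0.20 |
| 38 | 0 | 0.86 | 0.62 |
| 38 | 0.3 | 0.73 | 0.39 |
| 38 | 0.5 | 0.56 | 0.28 |
| 38 | 0.7 | 0.37 | 0.18 |

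The nominal levels for a single test are 0.05 and 0.025. Whatever the correlation, the expected number of false positives among 38 null tests is 38 × 0.05 = 1.9, of which 0.95 favour the training.

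**Adding the 6-month contrast.** Section {20a} names two contrasts, pre- to post-intervention and 6 months after surgery. For the 20 patient-reported scores (4 + 15 + 1) at two contrasts, with correlation 0.5 between scores and 0.5 between contrasts, simulation gives about 0.63 in either direction and 0.34 favouring the training. With both correlations at 0.7 the figures are 0.43 and 0.22.

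**The case against.** The best reply is that this is a condensed article, that hierarchies and false discovery procedures usually sit in an analysis plan, and that 0.05 is a conventional nominal level. The outcomes are labelled secondary, effect sizes will be given, and nothing says that a secondary result can rescue a negative primary. That would answer a complaint about missing detail. It does not answer a rule that the article itself states for all tests: an analysis plan that withheld significance claims from the secondary outcomes would be changing that rule.

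Several limits on the size of the problem do stand.

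- A reader might infer that a false benefit is likely, meaning more likely than not. The figures do not show this. For 38 tests at one contrast it is 0.18 to 0.39 for correlations from 0.7 to 0.3, and it passes one half only towards independence. Even the either-direction figure is below one half (0.37) at correlation 0.7.
- A reader might treat each of the four post-baseline visits as a separate test. For the 20 patient-reported scores that would give 0.84 in either direction at correlations of 0.5. The article names two contrasts; it says only that the mixed model uses the data from all visits.
- Half of the 38 are questionnaire scales (15 + 4 = 19) taken from a description of the instruments, which does not say that each will be tested. Hence the lower count of 18.
- The Objectives give no directional expectation for nutritional status, body composition or blood status.
- Proteomics and metabolomics are not in the outcome list, no group comparison of them is specified, and the number of analytes is not given. No count of false hits can be drawn from the document.

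It is also fair to say that calling results exploratory leaves the error rate as it is. What changes is that a nominal p-value no longer counts as a declared effect, and that is the defect here.

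**Conclusion.** The point holds as a matter of interpreting the secondary outcomes. With no effect and an assumed correlation of 0.5, the single-contrast chance of at least one significant secondary result is about 0.40 to 0.56 in either direction and 0.20 to 0.28 favouring the training, for 18 to 38 tests. It rises if the 6-month contrast is tested too. The exact size depends on the assumed correlations and on how the endpoints are counted, but every scenario shown is well above the nominal level. The primary test and the sample size are not affected.

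**What to change.** In section {20a}, limit the p ≤ 0.05 significance claim to the primary analysis. State that secondary outcomes will be reported as estimates with 95% confidence intervals and nominal p-values, and that these p-values will not be used to declare an effect.

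If the team wants a confirmatory secondary claim, name a short ordered list (for example one leg-strength, one fatigue and one quality-of-life score at T3), tested in sequence only if the primary is met. Because two primary outcomes are named, the text should say what counts as met.

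If the proteomic and metabolomic data are compared between groups, replace p ≤ 0.05 there with Benjamini-Hochberg control of the false discovery rate, for example at 5%.

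The change is wording only and needs no extra patients, visits or data. The downside is that isolated secondary p-values below 0.05 can no longer be presented as confirmed effects, and fewer proteomic or metabolomic features would be declared.

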### Interim analyses {21b}

An interim analysis will be performed after the first 10 participants have completed the exercise program and if it is registered that muscle mass is lower in the training group than in the control group the trial will be terminated.

### Methods for additional analyses (e.g., subgroup analyses) {20b}

For the primary outcome the model will, besides being adjusted for the baseline value, also be adjusted for diagnosis and type of surgery. Per protocol analysis for those who have adhered to the exercise program will be performed. Potential moderators of the exercise effect will be explored (e.g., age, sex, type of surgery, diagnosis). In addition, mediation analyses will be performed to explore potential underlying mechanisms of exercise effects (e.g., blood and muscle biomarkers). A subgroup analysis will also be performed to assess the rehabilitation effect only considering that some patients have a very limited time to exercise prior to surgery or may not be included until T2 due to very short time-to-surgery.

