### Trial design {8}

This Prev-Ex is a multi-center, two-armed randomized controlled trial (RCT) with 1:1 allocation ratio, stratified for research site, and testing the superiority of the intervention. Patients diagnosed with resectable pancreatic, biliary tract, and liver cancer are randomized to an exercise program consisting of home-based low-load BFR-T during both a pre- and postoperative period consisting of a total of 6–10 weeks, or a control group. Besides the nutritional support offered as standard care for these patients, protein supplementation will be given to both groups to ensure adequate protein intake. See Fig. 1 for the modified SPIRIT study flow chart.

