## Methods: participants, interventions, and outcomes

### Study setting {9}

Patients will be recruited from two sites: Karolinska University Hospital in Stockholm, Sweden, and Oslo University Hospital in Oslo, Norway. Testing of the participants’ physical fitness and body composition will take place in Stockholm at the research gym laboratory (Rörelseglädjelabbet), Karolinska University Hospital, and in Oslo at the exercise testing facilities at the Norwegian School of Sport Sciences.

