## Assignment of interventions: allocation

### Sequence generation {16a}

After baseline assessments, the participants are randomly allocated by the ALEA randomization software (ALEA Clinical Services B.V, 2023, The Netherlands) to either BFR-T or UC at a 1:1 ratio using a blocked computer-generated sequence.

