Due to the COVID-19 pandemic, the study start was delayed for almost 1 year. The initial plan was to include a more homogenous group: patients diagnosed with pancreatic or biliary tract cancer undergoing a pancreaticoduodenectomy; however, there were major challenges with the inclusion rate resulting in the study taking longer and risking a loss of statistical power. Amendments were made to the original plan to expand the inclusion criteria to patients undergoing either pancreaticoduodenectomy or laparoscopic surgery and to also patients with malignancies in the liver amendable for surgical resection. These changes were approved by the Swedish Ethical Review Authority and the Norwegian Regional committees for medical and health research ethics. We are aware that this will result in a heterogeneous group of patients. There is considerably less risk of complications for patients undergoing laparoscopic surgery compared to a pancreaticoduodenectomy; however, these potential differences will be adjusted for in the statistical analysis. Moreover, time to surgery and post-surgery recovery are similar across the diagnoses. In this study, we decided to include any patient who is diagnosed with resectable pancreatic, biliary tract, or liver cancer regardless of time-to-surgery which means that some patients will only have time to perform (T0) before surgery, while some will perform both (T0) and (T1). In some cases, time-to-surgery is only a few days which means that inclusion is not possible at (T0) but will instead take place at (T2). The reason for including patients at (T2) is that time-to-surgery is significantly shorter at the Norwegian site; consequently, amendments to the original plan had to be made to accommodate for the reduced time-to-surgery. We will perform a subgroup analysis to evaluate the rehabilitation effect (T2 to T3). Other amendments to the original plan include the addition of digitally supervised exercise and an exercise diary to be able to monitor exercise adherence more efficiently.

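### Randomisation is stratified by research site, but no stated model contains a site term; if site is prognostic, the reported standard errors are too large and the test is conservative

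*Protocol article*

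**What the plan says.** Trial design {8} describes a "two-armed randomized controlled trial (RCT) with 1:1 allocation ratio, stratified for research site, and testing the superiority of the intervention". Study setting {9} names the two sites, Stockholm and Oslo. Sequence generation {16a} says patients are allocated "to either BFR-T or UC at a 1:1 ratio using a blocked computer-generated sequence". It does not repeat the site stratum, but it does not contradict {8} either.

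For the analysis, Statistical methods {20a} states that "linear mixed modeling adjusted for baseline values (T0) of the outcome will be used to detect any significant differences between the two groups", with a group-by-time interaction as a fixed effect. Section {20b} then extends the model for the primary outcome: "For the primary outcome the model will, besides being adjusted for the baseline value, also be adjusted for diagnosis and type of surgery".

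The named terms are therefore group-by-time, the T0 value, diagnosis and type of surgery. Site is not named as a fixed or random effect in any model, and it is not among the examples of potential moderators in {20b}.

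The Discussion gives one reason to expect the sites to differ: "time-to-surgery is significantly shorter at the Norwegian site". It adds that entry at T2 was introduced for that reason.

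**The concern.** Stratified blocks balance the two arms within each site. A difference between sites in average outcome then largely cancels out of the group comparison. A model without site does not recognise this: it leaves the between-site variation in the residual, and the standard error is computed from that residual. If site is prognostic, the reported standard error exceeds the true sampling variability of the estimate. Confidence intervals are then wider than they need to be, and the test rejects less often than its nominal level.

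Site could plausibly matter for muscle size here. It is tied to the length of prehabilitation and to entry at T0 or T2, neither of which is captured by diagnosis or type of surgery. What is at stake is some power in a trial planned at 80% with 42 evaluable patients, and agreement between the analysis and the randomisation that was used.

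**Working it through.** **Inputs from the Protocol article.** Sample size {14}: difference 1 mm, standard error of measurement 0.8 mm, two-sided alpha 0.05, power 80%, 42 evaluable patients. Trial design {8}: 1:1 allocation, stratified by site. Study setting {9}: two sites.

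**Assumptions, because the documents give no figure.** R² is the share of outcome variance explained by site after the other covariates; it is set at 0, 0.05, 0.10 and 0.20. The 42 patients are split 22/20 between sites, with 28/14 as a check. Block size is 4. The comparison is simplified to one post-baseline difference between arms, not the full repeated-measures model.

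**Step 1: reproduce the planned number.** Taking the SD of a change as 0.8 × √2 = 1.131 mm,

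n per arm = 2 × SD² × (1.96 + 0.84)² / difference² = 2 × 1.28 × 7.85 / 1 = 20.1, rounded up to 21, so 42 in total.

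This matches the plan. Using 0.8 mm directly as the SD gives 22 in total, which does not. Power at 21 per arm is 0.817 by the normal approximation and 0.798 by the t distribution.

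**Step 2: effect on the reported standard error.** With site in the model, the residual SD is 1.131 × √(1 − R²). The ratio of the standard error reported without site to that with site is 1/√(1 − R²):

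- R² = 0.05: 1/√0.95 = 1.026
- R² = 0.10: 1/√0.90 = 1.054
- R² = 0.20: 1/√0.80 = 1.118

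In millimetres at R² = 0.10: without site, 1.131 × √(2/21) = 0.349; with site, 1.131 × √0.90 × √(2/21) = 0.331.

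**Step 3: true variability of the estimate.** In a simulation of 42 patients balanced within site at R² = 0.10, the empirical SD of the group estimate was 0.330 mm without site and 0.332 mm with it. The average reported standard errors were 0.348 and 0.329 mm. The estimate itself is no noisier; only the reported error is too large.

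**Step 4: type I error and power.** Simulation with site-stratified blocks, split 22/20, total SD held at 1.131 mm (100,000 trials per setting for type I error, 40,000 for power):

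| Assumed R² | Type I error, site omitted | Type I error, site included | Power, site omitted | Power, site included |
|---|---|---|---|---|
| 0 | 0.051 | 0.051 | 0.796 | 0.794 |
| 0.05 | 0.043 | 0.049 | 0.802 | 0.815 |
| 0.10 | 0.039 | 0.050 | 0.805 | 0.837 |
| 0.20 | 0.028 | 0.049 | 0.820 | 0.878 |

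The t-based formula with one degree of freedom spent on site gives 0.798, 0.817, 0.837 and 0.877 for the last column. With a 28/14 split the results barely move: at R² = 0.20, type I error without site is 0.030, and power is 0.823 without site against 0.877 with it.

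The power forgone is 0.815 − 0.802 = 0.013, 0.837 − 0.805 = 0.032 and 0.878 − 0.820 = 0.058, that is, about 1, 3 and 6 percentage points. Power without site does not fall as R² rises. The total SD is held fixed, so a larger site share means less variation within site.

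**The case against.** The strongest reply is that the harm is small and conditional. The relevant R² is what site explains after baseline muscle size, diagnosis and type of surgery. Adjusting for baseline would absorb much of any constant offset between the two laboratories, and at R² = 0 nothing is lost. A shorter wait for surgery in Norway shows a different exposure to prehabilitation; it does not show that site predicts muscle size given baseline. The article is also condensed, and {20b} does not call its covariate list exhaustive. All of this stands as a limit on size. It does not remove the point: the article chose to name its covariates, and the only stratification factor it declares is not among them.

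A reader might infer four stronger things that the documents do not support.

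- **That omitting site amounts to discarding 5%, 10% or 20% of the patients.** That describes the width of the reported interval, not power. At R² = 0.10, simulated power without site was 0.808, against 0.795 for a site-adjusted analysis of 10% fewer patients. At R² = 0.20, it was 0.822 against 0.792 for 20% fewer. (These come from a separate simulation run, so they differ slightly from the table.)
- **That the estimate is biased or false positives become more likely.** Neither follows. Type I error is at or below nominal.
- **That the different strength-testing devices at the two sites bear on the primary analysis.** Strength is a secondary outcome. The primary outcomes are measured by ultrasound, for which no site difference is described.
- **That adjusting for type of surgery conditions on an event after randomisation.** This would need the covariate to be the operation performed. No section says so, and whether the planned or the performed operation is coded is a definition an article may leave to the full protocol.

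**Conclusion.** The point holds as a modest one. The randomisation is stratified by site and the stated models omit site. The estimate is unbiased, its true variability is essentially unchanged, and type I error is not inflated. If site is prognostic beyond the listed covariates, the analysis is conservative: at an assumed R² of 0.05 to 0.20 the reported standard error is about 3% to 12% too large, and power is about 1 to 6 points below what a site-adjusted analysis would give. At R² = 0 there is no loss. The site-omitted analysis stays at about the planned 80% across the range, so what is given up is an available gain.

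These sizes rest on the assumed R², an SD of 1.131 mm, 42 evaluable patients and a single-comparison simplification of the mixed model. The direction of the effect does not depend on the particular R² chosen.

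**What to change.** Add research site as a fixed effect to the primary-outcome mixed model in {20b}, alongside the T0 value, diagnosis and type of surgery. Do the same in the secondary longitudinal models under {20a} for outcomes measured at both sites. Muscle biopsy and dual x-ray absorptiometry outcomes, collected only at the Norwegian site, need no site term. Record the change before outcome data are analysed, so that it cannot depend on the results.

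The cost is one degree of freedom per model. Site is already known for every patient. If site turns out not to be prognostic, the price is negligible: simulated power at R² = 0 is 0.794 with the term and 0.796 without it.

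### Allocation is stratified by site but site is not in the stated primary model; if site still predicts muscle change after adjustment, the test is conservative and loses some power

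*Protocol article*

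**What the plan says.** Under Trial design {8}, the protocol article describes a two-arm trial "with 1:1 allocation ratio, stratified for research site, and testing the superiority of the intervention". Study setting {9} names one Swedish and one Norwegian hospital. Sequence generation {16a} says that patients are allocated "to either BFR-T or UC at a 1:1 ratio using a blocked computer-generated sequence" and does not repeat the stratification.

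The analysis is described in two places. Statistical methods {20a} says that "linear mixed modeling adjusted for baseline values (T0) of the outcome will be used to detect any significant differences between the two groups", and adds: "Group-by-time interaction will be included as a fixed effect". Methods for additional analyses {20b} completes the covariates: "For the primary outcome the model will, besides being adjusted for the baseline value, also be adjusted for diagnosis and type of surgery". Site is not a fixed effect, a random effect or a stratum in any model, and it is not among the examples of moderators to be explored.

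The Discussion reports that "time-to-surgery is significantly shorter at the Norwegian site" and gives this as the reason for letting some patients enter only after surgery. The oversight section says that testing, including muscle ultrasound, takes place in a separate laboratory at each site.

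**The concern.** Stratifying by site balances the arms within each site, so a difference in mean outcome between sites largely cancels from the treatment comparison. The estimate becomes more precise, but the analysis shows this only if the model knows about site. Without a site term, between-site variation stays in the residual (in a mixed model, mostly in the between-patient variance) and the reported standard error describes a noisier comparison than the one carried out. Confidence intervals are then too wide, the true type I error is below the nominal 5%, and power gained by design is not used. The sample size calculation aims at 80% power, so the trial has little in reserve.

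**Working it through.** **Inputs from Sample size {14}.** Two-sided alpha 0.05, power 80%, effect 1 mm in muscle thickness, standard error of measurement 0.8 mm, 42 evaluable patients.

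**Assumptions, not in the document.** The gap *g* between sites in mean change (in mm, the same in both arms, remaining after the other covariates), the share *q* of patients at one site, and a block size of 4 in the simulations.

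**Step 1: reproduce 42.** Taking 0.8 mm directly as the SD gives 2 × (1.96 + 0.84)² × 0.8² / 1² ≈ 10.0, rounded up to 11 per arm or 22 in total, which does not match. Taking the SD of a difference between two measurements, 0.8 × √2 = 1.131 mm, gives 2 × (1.96 + 0.84)² × 1.28 / 1² ≈ 20.1, rounded up to 21 per arm or 42 in total, which matches. So 1.13 mm is the SD implied by the calculation; the text does not state it.

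**Step 2: true and reported standard error.** With balance within site, the true SE does not depend on *g*:

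- True SE = 1.131 × √(2/21) = 0.349 mm.
- Without a site term, the residual SD is about √(1.131² + q(1 − q)g²).
- With q = 0.5 and g = 0.5 mm: √(1.28 + 0.0625) = 1.159, so the reported SE is 1.159 × √(2/21) = 0.358 mm.
- With q = 0.5 and g = 1 mm: √(1.28 + 0.25) = 1.237, so the reported SE is 1.237 × √(2/21) = 0.382 mm.

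**Step 3: type I error.** The critical t value on 40 degrees of freedom is 2.021. Too large a reported SE raises the effective threshold by the ratio of the two SEs:

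- g = 0.5 mm: 2.021 × 0.358/0.349 ≈ 2.07, so type I error is about 4.5%.
- g = 1 mm: 2.021 × 0.382/0.349 ≈ 2.21, so type I error is about 3.3%.

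**Step 4: power for a 1 mm effect.** Simulated trials with blocks within site, N = 42, SD 1.131 mm, site splits 50:50 and about 70:30, analysed by a linear model of change with and without site:

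| Assumed site gap | Power without site | Power with site | Type I error without site |
|---|---|---|---|
| 0 | 80% | 80% | about 5% |
| 0.5 mm | 78–79% | 80% | about 4.5% |
| 1.0 mm | 73–75% | 80% | about 3–3.6% |

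With site in the model, type I error stays at about 5% throughout.

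**Step 5: sensitivity to the SD.** The SD of 1.13 mm reflects measurement error alone. If patients also differ in true change and the SD is, say, 2 mm (assumed), a 1 mm gap with a 50:50 split costs about 2 points (33% against 35%), with type I error about 4.5%. The low power in that case comes from the larger SD, not from omitting site.

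These figures compare one change score. The planned model uses several visits, so they show direction and approximate size; they do not predict the result of the mixed model.

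**The case against.** The strongest reply is that the loss is conditional. It needs a site effect that survives adjustment for baseline, diagnosis and type of surgery, and the document quantifies none. Three parts of this reply stand.

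- A constant offset between laboratories is largely removed by adjusting for baseline thickness. Only a difference in change between sites matters.
- Shorter time to surgery in Norway shortens prehabilitation, and only the exercise arm trains. Part of the site effect may therefore be a difference in treatment effect between sites, which a main-effect term does not model.
- A 1 mm gap equals the whole effect the trial is powered to detect.

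It can also be said that a journal article need not list every model term. That carries less weight here, because the article does list the covariates for the primary outcome and leaves out the only stratification factor it names. That Sequence generation {16a} does not repeat the stratification does not remove the point either, since Trial design {8} states it plainly.

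A reader might infer that site is certainly prognostic, so that the standard error will definitely be wrong. The document does not support that: it gives reasons to expect a site effect, not evidence of one. Nor should a reader infer a biased estimate or an inflated false-positive rate; the error runs in the conservative direction.

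**Conclusion.** The stated primary analysis leaves out the factor by which the trial randomises. This is an inconsistency between design and analysis, and its consequence is one of efficiency. The loss ranges from nothing, through 1 to 2 power points at a 0.5 mm gap, to about 6 to 7 points in the extreme case of 1 mm. The range rests on the inferred SD of 1.13 mm, an additive site gap common to both arms, and no absorption of that gap by diagnosis or type of surgery. A larger SD or such absorption would reduce the loss. The change is worth making because it costs almost nothing and, made before the data are analysed, it removes a later choice between models with and without site.

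**What to change.** Add site (Sweden or Norway) as a fixed effect in the linear mixed models for muscle thickness and cross-sectional area, and in those for secondary outcomes analysed by mixed model and collected at both sites. Name it in Statistical methods {20a} and Methods for additional analyses {20b} as the stratification factor. Hospitalization, which is analysed by chi-squared test and odds ratio, and outcomes collected only in Norway (biopsy, dual x-ray absorptiometry) fall outside this change. The cost is one degree of freedom, and the variable is already known for every patient.
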